## Methods/design

The multicentre parallel cluster randomised controlled trial (RCT) will comprise 12 maternity sites with a primary objective of determining burnout levels of midwives in relation to the provision of Group Clinical Supervision (GCS), the intervention. Secondary objectives will be measuring perceptions of workplace culture and the efficacy of the GCS intervention itself in relation to GCS. Staff attrition and sick leave rates of midwives will also be measured during the study period.

It is hypothesised that regular GCS will improve midwives’ perceptions of their workplace culture and lower their levels of work-related burnout (primary outcome); that midwives with positive perceptions of their workplace culture will be more likely to remain in their profession; and maternity units that support midwives to attend regular GCS will have lower levels of midwifery staff attrition and sick leave than those that do not (secondary outcome).

Quantitative and qualitative data will be collected in this study. Validated quantitative tools will be used: the Australian Midwifery Workplace Culture (AMWoC) instrument [37], the Copenhagen Burnout Inventory (CBI) [38] and the Clinical Supervision Evaluation Questionnaire (CSEQ) [39] (intervention sites only). These are described more fully below. The survey platform REDCap ([Research Electronic Data Capture] a secure web application for building and managing online surveys and databases) will be used.

Participants in the intervention sites will be requested to attend GCS sessions as much as is practicable, but at least twice in a six-month period. Surveys will be emailed to participants every six months that contain the tools listed above, and simple demographic/workplace questions. Participant surveys in control sites will not contain the CSEQ. The number of GCS sessions or other supportive strategies (such as mentoring/coaching) that all participants have undertaken will be measured. The CONSORT statement for cluster RCTs will be used to ensure rigour and process [40].

### Governance

Governance of the study will be undertaken through a Trial Steering Committee (TSC) comprising an experienced Trial Specialist, biostatistician, midwife, a Principal Investigator (of one of the maternity sites), research assistant, Chief Investigator and an independent^2^ Chair. The role of the Steering Committee is to provide overall supervision of the study, to monitor and supervise the progress of the study towards achieving its objectives. The Committee will concentrate on the progress of the study, adherence to the protocol, safety of the midwives and consideration of new information relevant to the research question. They will also monitor recruitment rates, develop strategies to deal with any recruitment issues and approve any amendments that need further ethical authorisation.

Members of the TSC will be offered authorship of all publications, of which there are no restrictions. A publication plan has been disseminated to the TSC and the Principal Investigators with a timeframe and explanation of what authorship means. All results will be published regardless of the magnitude or direction of effect. This will involve journal publications and conference presentations, as well as reports to the Local Health Districts and/or Ministry of Health, NSW. No professional medical writers will be employed.

### Setting

The study will recruit twelve [12] predominantly Sydney-based (Australia) public maternity sites to the cluster RCT (not private facilities). Within these sites, we will recruit around 75 midwives per site (*n* = 894), a reasonable number given the numbers of midwives employed at the participating institutions. The maternity sites are Sydney-based for logistical reasons as the GCS facilitators plan to deliver the monthly Group Clinical Supervision sessions face-to-face.

### Recruitment process

Potential participants will comprise all Registered Midwives (except those in management/senior roles or agency midwives) from the participating maternity sites within Sydney and surrounds. Engagement with the Directors of Nursing and Midwifery and the Midwifery Unit Managers of antenatal, postnatal and intranatal areas of the maternity units will be undertaken, with named Principal Investigators (PIs) at each site. The PIs will contact the eligible midwives via email and through staff meetings to inform them about the study. The Midwifery Unit Managers will be reminded by the PIs of the sessions each month – so that they may release the staff from workplaces/arrange cover in order for them to attend the GCS sessions.

Multiple sessions will be held at the maternity sites to discuss the study with midwives. This will contain information about GCS and its potential benefits to the participants, and the completion of six-monthly surveys. Flyers for the study will be placed in maternity site tearooms and other high traffic areas for midwives in the maternity units. The dates and times of the GCS sessions will be co-created with each maternity site, and these may change over the course of the study to help midwives from different maternity areas participate and attend the GCS sessions. Close attention will be paid to this part of the study to ensure the highest level of participation.

Following consent, ethical approval, randomisation and extensive site liaison, the PIs at the intervention sites will alert eligible participants (midwives) and encourage attendance at the study GCS sessions on-site every month. All participants will be sent an online survey to complete at the beginning of the study and every six months during the study data collection period (planned for May 2022 – November 2024). Study information and consent for participants to complete the survey will be embedded into the online platform prior to commencement. Hardcopies of the survey will also be available for completion by participants.

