### Participant information and consent

The study will be conducted in compliance with all stipulations of this protocol, the conditions of ethics committee approval, the NHMRC National Statement on Ethical Conduct in Human Research [41] and the Note for Guidance on Good Clinical Practice (CPMP/ICH-E6(R2). Participants will be provided with complete information regarding the study through the Participation Information Statement, via the Principal Investigator for the site (senior Registered Midwives), the research assistant or Chief Investigator. They will be given information about the Group Clinical Supervision (GCS) intervention and the voluntary nature of attending sessions and completing the 6-monthly surveys. Distress protocols have been formulated for use by the GCS facilitators, and Employee Assistance Program telephone numbers (for free counselling) will be embedded into the online survey and stated on the hardcopy version. Should any harms to participants occur, these will be brought to the attention of the TSC for discussion, guidance and reporting. Given the nature of the Group Clinical Supervision intervention, there are few harms anticipated for participants. Should participants feel they do not benefit from the sessions, they simply will not attend. Harms for the Group Clinical Supervision facilitators will be mitigated through monthly sessions with their own Clinical Supervisor. Should any harms to participants occur, these will be brought to the attention of the TSC for discussion, and reporting.

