### Intervention – group clinical supervision

The intervention in this study is the provision of monthly GCS (by two trained Clinical Supervision facilitators) in the intervention units for up to two years. This is compared to maternity sites with no monthly GCS offered to midwives. Different to supervision of clinical skills, preceptorship, mentoring and coaching, Clinical Supervision is a structured supportive session lasting up to 90 min with a skilled facilitator that allows participants to deeply reflect on their professional lives. The Australian Clinical Supervision Association defines Clinical Supervision as ‘a formal professional relationship between two or more people in designated roles, which facilitates reflective practice, explores ethical issues and develops skills’ [42].

Group Clinical Supervision will be standardised through only two facilitators delivering the intervention throughout the study period (trained in the endorsed Role Development Clinical Supervision model) [43]. Attendance will be optional but strongly encouraged for midwives to reflect on their practice in a safe, confidential and supportive environment. Control sites will have no GCS sessions, but midwives will be recruited to complete the online (or hardcopy) survey tools every six months for the study period.

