### Randomisation

Once recruited and ethical clearance gained, the lead CI will perform simple randomisation of the maternity sites to either the intervention or control arm via a computerised method. Those in the intervention arm will receive monthly GCS in their maternity units, and those in the control arm will not. The study design and nature of the intervention means that blinding for staff will not be possible.

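### The protocol does not require midwives to enrol and complete the baseline burnout survey before their site's allocation is known, and its natural reading is that they do so afterwards

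*Protocol article*

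**What the plan says.** All statements are from the protocol article.

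- **Randomisation.** The conditions for allocating sites are given as "Once recruited and ethical clearance gained, the lead CI will perform simple randomisation of the maternity sites". Midwife enrolment and a completed baseline survey are not named. The same section says "The study design and nature of the intervention means that blinding for staff will not be possible".
- **Recruitment process.** After the randomisation step, the text reads "Following consent, ethical approval, randomisation and extensive site liaison, the PIs at the intervention sites will alert eligible participants (midwives"; the sentence goes on to say that these midwives will be encouraged to come to the monthly sessions. Next come "All participants will be sent an online survey to complete at the beginning of the study and every six months during the study data collection" and "Study information and consent for participants to complete the survey will be embedded into the online platform prior to commencement". Earlier in the section, principal investigators at every site tell eligible midwives about the study by email and at staff meetings. Of the on-site information sessions it says "This will contain information about GCS and its potential benefits to the participants, and the completion of six-monthly surveys". No date relative to allocation is given for any of this.
- **Intervention.** "Control sites will have no GCS sessions, but midwives will be recruited to complete the online (or hardcopy) survey tools".
- **Participant information and consent.** Midwives are told of "the voluntary nature of attending sessions and completing the 6-monthly surveys".
- **Data collection and management.** Completed consent forms are scanned into REDCap, with no statement of when they are signed.
- **Statistical analysis.** The primary outcome is the percentage of midwives with moderate or higher burnout on the self-completed CBI. The section says that confounding is not expected because of randomisation, and that key variables with large imbalances will be added to the model.

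**The concern.** Randomising sites balances the pools of eligible midwives in expectation. It does not balance the midwives who choose to join once they know what their site has been given. At an intervention site a midwife joins a study that offers her supervision. At a control site she joins a series of surveys. More stressed or more engaged midwives could respond differently to those two offers, and the burnout comparison would then carry a difference that supervision did not cause.

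A second route is the baseline answer itself. A self-reported CBI completed with the arm known may be coloured by relief or disappointment, and is then not a clean pre-allocation measure.

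The listed safeguards do not reach this:

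- Intention to treat protects the comparison among those enrolled, not the choice of who enrols.
- Multiple imputation is planned for missing data and is not described as covering people who never joined.
- A blinded biostatistician changes neither route.
- Adjustment for large imbalances covers measured variables only.

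**Working it through.** **1. Order of steps, set side by side**

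| Step | Position in the text | How firm |
|---|---|---|
| Site recruitment and ethics clearance | Before randomisation | Stated, if the recruitment meant is that of sites |
| General information to midwives at all sites | No position given | Open |
| Alert and encouragement to attend, intervention sites | After randomisation | Stated |
| Midwife's consent to the survey | In the survey platform | Stated for the online survey; timing of paper forms open |
| Baseline CBI | Start of the study, described after the randomisation step | Natural reading, not stated outright |
| Recruitment of control midwives | Described for sites already called control | Natural reading |

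**2. The plan's own sample size**

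Inputs from the Sample size section: 67% burnout, a 15% decrease, α 0.05, 80% power, 62 midwives per site, ICC 0.02. Two readings are mine, chosen because they reproduce the figure: the decrease is absolute (67% to 52%) and the test is two-sided.

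- Individually randomised size, pooled-variance formula without continuity correction: [1.96·√(2·0.595·0.405) + 0.842·√(0.67·0.33 + 0.52·0.48)]² / 0.15² ≈ 167 per arm.
- Design effect: 1 + (62 − 1)·0.02 = 2.22.
- 167 × 2.22 ≈ 371 per arm, about 742 in total, against 744 stated. Power at 373 per arm is 80.3%.

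The figure reproduces. The point about order does not change it.

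**3. What a selection gap would do**

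The gap sizes are assumptions; the protocol gives none. Let d be the difference between arms in the analysed burnout percentage, with no treatment effect and after whatever adjustment is made. Using 744/2 = 372 per arm and a mean prevalence of 0.645 (midway between 67% and 62%):

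SE = √(2 · 0.645 · 0.355 · 2.22 / 372) = 0.0523, and λ = d / SE.

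The false-positive rate is the two-sided rejection probability at shift λ, from a non-central t with 12 − 2 = 10 degrees of freedom, or from the normal. The last column is power against a true 15-point drop when the gap works against it (formula of step 2, normal test, 373/2.22 effective midwives per arm).

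| d | Share of 15-point target | λ | False positives, t(10) | False positives, normal | Power if the gap opposes the effect |
|---|---|---|---|---|---|
| 0 | 0% | 0 | 5% | 5% | 80% |
| 3 points | 20% | 0.57 | 8.2% | 9% | 62% |
| 5 points | 33% | 0.96 | 14.0% | 16% | 47% |
| 7.5 points | 50% | 1.43 | 25.5% | 30% | 30% |

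**4. How uneven joining would have to be**

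Again an assumption. True burnout is 67% in both arms, and joining in the control arm does not depend on burnout.

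- Intervention arm, burned-out midwives join at 50% and others at 60%: 0.67·0.50 / (0.67·0.50 + 0.33·0.60) = 0.335/0.533 = 62.9%, about 4 points below 67%.
- Intervention arm, 60% and 50%: 0.402 / (0.402 + 0.165) = 70.9%, about 4 points above.

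A ten-point difference in joining rates thus produces a gap inside the range of step 3, in either direction. Colouring of the baseline answers is not quantified.

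**The case against.** The strongest reply is that the order is not fixed as the concern supposes.

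- The sentence about alerting midwives concerns attendance at sessions. A reader might infer from it that midwives first hear of the study after allocation. The text does not support that: general information goes to eligible midwives at all sites, with no stated timing.
- A reader might also infer that the protocol states outright that consent and baseline come after allocation. It does not. The same sentence puts consent ahead of randomisation without saying whose, the Randomisation section requires recruitment first, and the consent forms under Data collection and management could be signed at any point.
- Fig. 1, the study timeline, was not available for this review and may show where baseline falls.
- Nothing says that control midwives receive different study information.
- The analysis section does plan a baseline comparison, admits that cluster randomisation may leave individual covariates unbalanced, and adjusts for large imbalances.
- The gaps used above come from no document.

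Most of this stands as a limit on certainty. It does not remove the point. Being informed is not being enrolled, and no sentence places enrolment or baseline before allocation. If the early consent is the midwives' own, it must be reconciled with consent inside the survey and with recruitment at sites already called control; even then baseline has no stated place before allocation. Adjustment covers measured variables only, and a baseline CBI answered with the arm known may itself be affected.

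**Conclusion.** The point holds as a gap in the protocol with a likely, not certain, reading: enrolment and baseline burnout are not required to precede knowledge of allocation, and the Recruitment process, Intervention and Randomisation sections read most naturally as placing them after it. The assurance that randomisation makes confounding unlikely does not extend to selection after allocation.

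It would be tempting to conclude that the burnout comparison is biased, or to take the 8–26% (t) or 9–30% (normal) false-positive range as an estimate. The documents support neither. The range shows only what assumed gaps of 3 to 7.5 points would do under the protocol's own ICC and cluster size; actual direction and size are unknown. This is a validity risk to the primary comparison that can be avoided cheaply, not a demonstrated error.

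**What to change.** - At all 12 sites, list the eligible midwives, give every site the same study information, and close consent and the baseline survey before allocation is generated or disclosed.
- Define the primary analysis population as midwives enrolled before disclosure, and report later joiners separately.
- Say whose consent and whose recruitment precede randomisation, and when the consent forms are signed, so that the sections agree. If enrolment and baseline already came first, one sentence saying so settles the point.
- If midwives have already enrolled after disclosure, report response against the eligible staff list by arm and remove the statement that confounding is not expected.

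**Cost.** Supervision starts somewhat later; the protocol gives no basis for saying by how much, since about 75 midwives per site (894 in all) are sought. Midwives who join later drop out of the primary analysis, so any site short of its target at closure costs power.

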### Participant information and consent

The study will be conducted in compliance with all stipulations of this protocol, the conditions of ethics committee approval, the NHMRC National Statement on Ethical Conduct in Human Research [41] and the Note for Guidance on Good Clinical Practice (CPMP/ICH-E6(R2). Participants will be provided with complete information regarding the study through the Participation Information Statement, via the Principal Investigator for the site (senior Registered Midwives), the research assistant or Chief Investigator. They will be given information about the Group Clinical Supervision (GCS) intervention and the voluntary nature of attending sessions and completing the 6-monthly surveys. Distress protocols have been formulated for use by the GCS facilitators, and Employee Assistance Program telephone numbers (for free counselling) will be embedded into the online survey and stated on the hardcopy version. Should any harms to participants occur, these will be brought to the attention of the TSC for discussion, guidance and reporting. Given the nature of the Group Clinical Supervision intervention, there are few harms anticipated for participants. Should participants feel they do not benefit from the sessions, they simply will not attend. Harms for the Group Clinical Supervision facilitators will be mitigated through monthly sessions with their own Clinical Supervisor. Should any harms to participants occur, these will be brought to the attention of the TSC for discussion, and reporting.

### Intervention – group clinical supervision

The intervention in this study is the provision of monthly GCS (by two trained Clinical Supervision facilitators) in the intervention units for up to two years. This is compared to maternity sites with no monthly GCS offered to midwives. Different to supervision of clinical skills, preceptorship, mentoring and coaching, Clinical Supervision is a structured supportive session lasting up to 90 min with a skilled facilitator that allows participants to deeply reflect on their professional lives. The Australian Clinical Supervision Association defines Clinical Supervision as ‘a formal professional relationship between two or more people in designated roles, which facilitates reflective practice, explores ethical issues and develops skills’ [42].

Group Clinical Supervision will be standardised through only two facilitators delivering the intervention throughout the study period (trained in the endorsed Role Development Clinical Supervision model) [43]. Attendance will be optional but strongly encouraged for midwives to reflect on their practice in a safe, confidential and supportive environment. Control sites will have no GCS sessions, but midwives will be recruited to complete the online (or hardcopy) survey tools every six months for the study period.

### Outcome measures

Every six months, the following will be collected: simple demographic information as well as midwifery qualifications, area of primary work, years of service, intention to leave position or profession and number of GCS or other support sessions attended. In addition, workforce data on midwifery staff turnover and sick leave will be collected from the Local Health District workforce departments at each six month period.

*The Australian Midwifery Workplace Culture (AMWoC) instrument* is a 22 item, 6-point Likert scale questionnaire that measures midwives’ perceptions of their workplace culture. Psychometrically tested, it can contribute to understanding the dimensions of a midwifery work environment, including problematic practices and attitudes [37]. Qualitative data will be collected from an open-ended question added to the AMWoC instrument requesting participants to expand on perceptions of their workplace culture.

*The Copenhagen Burnout Inventory (CBI)* is an extensively used 19-item, 5-point Likert scale that measures personal (6 items), work-related (7 items) and client-related levels of burnout (6 items) [38].

*Clinical Supervision Evaluation Questionnaire (CSEQ)* is a validated 14-item questionnaire on a 5-point Likert scale related to three dimensions: the purpose, process and impact of Clinical Supervision [39].

### Sample size

Assuming that 67% of midwives will have moderate or high levels of burnout [18], a sample size of 744 (373 per arm) from twelve maternity sites with an average of 62 midwives per site will achieve 80% power to detect a 15% decrease in moderate or greater burnout with an α level of 0.05 and intra-class correlations of 0.02. Assuming 20% attrition, the target sample size is 894 (447 midwives). This equates to an average of 75 midwives per site.

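### The stated 80% power makes no allowance for having only 12 randomised sites; an unadjusted 6 v 6 comparison at a valid 5% level has about 71–72%, for a fall of 15 percentage points

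*Protocol article*

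**What the plan says.** The Sample size section starts from a burnout prevalence: "Assuming that 67% of midwives will have moderate or high levels of burnout". It then gives "a sample size of 744 (373 per arm) from twelve maternity sites", "with an average of 62 midwives per site", and claims that this "will achieve 80% power to detect a 15% decrease in moderate or greater burnout" "with an α level of 0.05 and intra-class correlations of 0.02". It adds 20% for attrition, for a target of 894. It does not say whether the 15% is absolute or relative, or whether α is two-sided.

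The Abstract (Methods) assigns half of the twelve sites to the intervention, so 6 v 6. The Statistical analysis section names logistic regression by generalised estimating equations (GEE) as the main analysis. The article mentions neither a small-sample correction nor a reference distribution for the test.

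**The concern.** Sites, not midwives, are randomised. With six sites per arm, the between-site variance is estimated from 12 sites and leaves about 10 degrees of freedom. The two-sided 5% critical value is then 2.23, not 1.96. A normal-theory formula with a design effect corrects for the correlation within sites but not for the small number of sites, so it overstates power.

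The effect is also worded loosely. A fall of 15% from 67% could mean 67% to 52%, or 67% to 56.95%.

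At stake is how a null result is read. Readers would set it against a 20% chance of missing the target effect, when that chance is nearer 28%.

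**Working it through.** **Inputs.** From the Sample size section: control rate 0.67, 62 midwives per site, ICC 0.02, α 0.05. From the Abstract: six sites per arm, so 6 × 62 = 372 per arm (the text prints 373). Two-sided testing and equal site sizes are inferred, because they reproduce the stated size.

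**1. Reproduce the stated figure.**
- Design effect = 1 + (62 − 1) × 0.02 = 2.22.
- Standard two-proportion formula, 67% v 52%, two-sided 5%, 80% power: 166.9 per arm. Multiplied by 2.22, this is about 371 per arm, against 373 stated.
- Standard error = √[(0.67 × 0.33 + 0.52 × 0.48) × 2.22 / 372] = 0.0530.
- λ = 0.15 / 0.0530 = 2.83.
- Normal power = Φ(2.83 − 1.96) = 80.8% (79.9% with pooled variance).

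The 80% is therefore correct under this formula. Variants that do not reproduce the size: one-sided 5% needs 293 per arm, a continuity correction needs 402, and a relative 15% fall (67% to 56.95%) needs about 810.

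**2. Allow for 12 sites.** Keep the same standard error and λ, but refer the statistic to t with 2 × 6 − 2 = 10 degrees of freedom (critical value 2.23). Noncentral t gives:

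| Case, 67% v 52% | Power |
|---|---|
| 62 per site, unpooled variance | 72.3% |
| 62 per site, pooled variance | 71.3% |
| 894 less 20% = 715 analysed, 59.6 per site (unpooled) | 71.6% |

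Solving for the difference that gives 80% power on 10 degrees of freedom at 62 per site gives 16.5 percentage points.

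**3. Check by simulation.** Beta-binomial data, ICC 0.02, 62 per site, 6 v 6 sites, 100,000 runs:

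| Test | Power | Type I error at 67% |
|---|---|---|
| t-test on site proportions, 10 df | 71.8% | 5.0% |
| GEE logit, corrected standard error, t on 10 df | 71.0% | 4.8% |
| GEE logit, uncorrected sandwich, z test | 83.4% | 10.2% |

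The two tests that hold the 5% level have 71–72% power. The test that passes 80% has about twice the stated α.

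**4. Sensitivity to site size (assumed).** The article gives only an average site size. With design effect 1 + [(1 + CV²) × 62 − 1] × 0.02 and an assumed coefficient of variation (CV) of 0.5, the design effect is 2.53 and power on 10 degrees of freedom is 66.7%. At CV 0 it is 72.3%. The value 0.5 is illustrative and does not come from the protocol.

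**The case against.** **There is no arithmetic error.** This stands. The inputs give the stated size. The fault is the choice of a large-sample formula for 12 randomised units.

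**The planned analysis is not an unadjusted single comparison.** This stands in part. The protocol plans a baseline survey, six-monthly repeats, adjustment for a stratification variable and the addition of imbalanced covariates. A variance reduction of about 20% would restore 80% power (81.3% on 10 degrees of freedom, 80.4% on 9). But the article does not commit to adjusting for baseline burnout and gives no correlation from which to derive such a reduction. Site-level covariates also cost degrees of freedom: on 9, with no variance gain, power is 70–71%. The loss may be partly recovered, but by how much cannot be said.

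**Uncertainty in the ICC matters as much.** True: on 10 degrees of freedom an ICC of 0.015 gives 78% and 0.013 gives 81%. But the claim is made at an ICC of 0.02, and at that value it does not hold.

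**A small-sample correction belongs in the analysis plan.** Its absence from the article is no fault. It does not rescue the 80%, however, because a valid correction is what brings power down to about 72%.

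A reader might infer two stronger points. The first is that the trial will run at a 10% type I error. The article does not fix the variance estimator or the reference distribution, so this does not follow; only the pairing of 80% power with α 0.05 fails. The second is that power is really about 48% (normal) or 41% (10 degrees of freedom), which is the relative reading. That reading does not reproduce 744, so the wording is ambiguous, and these figures do not describe the trial as planned.

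**Conclusion.** The concern holds in a limited form. The stated 80% power and α of 0.05 cannot both be met by an unadjusted 6 v 6 comparison on the protocol's own inputs. Power at a valid two-sided 5% level is about 71–72%, roughly 8 points lower, and about 16.5 percentage points is detectable with 80% power.

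This rests on exactly six sites per arm, equal site sizes, an ICC of 0.02, one follow-up comparison, and no gain from baseline or repeated measures. Unequal sites would lower the figure; baseline adjustment may raise it. The scale of the 15% is a matter of wording: only percentage points fit the stated sample size.

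**What to change.** Rewrite the Sample size paragraph as follows:
- Give the effect as an absolute reduction of 15 percentage points, from 67% to 52%, and state that the test is two-sided.
- Give power as about 72% for six sites per arm on 10 degrees of freedom, or state that about 16.5 percentage points is detectable with 80% power.
- Say that this assumes equal site sizes and no gain from baseline or repeated measures. Add a figure for unequal sites with the coefficient of variation named as an assumption (about 67% at 0.5).
- If baseline adjustment is to be relied on to recover power, say so and give the assumed correlation and its source. Until then, say only that it may recover some of the loss.

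The cost is one paragraph and a less favourable stated power. No extra recruitment is proposed.

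### The recruitment target of 894 adds 20% to the required 744 rather than allowing for a 20% loss, so it covers only 16.8% attrition (minor)

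*Protocol article*

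**What the plan says.** The Sample size section of the protocol article starts from a burnout prevalence ("Assuming that 67% of midwives will have moderate or high levels of burnout") and sets out the requirement as "a sample size of 744 (373 per arm) from twelve maternity sites", with 62 midwives per site on average. This is said to give "80% power to detect a 15% decrease in moderate or greater burnout", "with an α level of 0.05 and intra-class correlations of 0.02".

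The attrition step follows: "Assuming 20% attrition, the target sample size is 894 (447 midwives"). The section then converts the target to an average of 75 midwives per site. The Setting section carries the same total of 894 into the recruitment plan: "we will recruit around 75 midwives per site".

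Neither section defines the 20% as anything other than attrition.

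**The concern.** Attrition of 20% ordinarily means that one in five of those recruited is lost, so the recruited number times 0.8 should equal the number needed for analysis. Here 894 × 0.8 is below 744. The target repeated in Setting therefore does not deliver the sample that the Sample size section says is needed, under that section's own attrition assumption.

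The stated power of 80% for the primary outcome depends on reaching 744, and the calculation leaves almost no margin above 80%. The same sentence also prints a per-arm figure that does not agree with its total.

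**Working it through.** **Inputs (Sample size section):** control proportion 0.67; decrease of 15%; α 0.05; power 0.80; intra-class correlation (ICC) 0.02; 12 sites; 62 per site; total 744; attrition 20%; target 894 (447). The abstract gives half the sites to each arm, so 6 per arm.

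**Assumptions needed:** the article does not say whether the 15% is absolute or relative, whether the test is two-sided, or which variance form was used. I take an absolute fall (67% to 52%) and a two-sided test with a normal approximation, because these reproduce 744. A relative 15% fall (67% to 56.95%) would need about 1,625 midwives at 62 per site.

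**1. Reproduce 744.**
- Pooled-variance formula per arm, before clustering, with p̄ = 0.595: n = [1.96·√(2·0.595·0.405) + 0.8416·√(0.67·0.33 + 0.52·0.48)]² / 0.15² = 166.9, so 167.
- Design effect: 1 + (62 − 1) × 0.02 = 2.22.
- 167 × 2.22 = 370.7 per arm, 741 in total; as 12 whole sites of 62, 12 × 62 = 744.

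The requirement of 744 is reproduced.

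**2. Reproduce 894.**
- Multiplying by 1.2, by arm: 372 × 1.2 = 446.4, rounded up to 447; 2 × 447 = 894. This matches exactly.
- On the total: 744 × 1.2 = 892.8, or 893, so the rounding was probably done by arm.
- Dividing by 0.8: 744 / 0.8 = 930 (465 per arm, 77.5 per site). This does not match.

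**3. What 894 delivers.**
- 894 × 0.8 = 715.2, about 715 (715.2 / 12 = 59.6 per site); 744 − 715 = 29 short.
- Attrition that 894 does cover: 1 − 744/894 = 0.168.
- With the rounded 75 per site: 12 × 75 = 900; 900 × 0.8 = 720 (60 per site); 24 short.

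**4. Effect on power.** The effective number per arm is 6m / [1 + (m − 1) × 0.02], where m is the number analysed per site.

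| Analysed | m | Design effect | Effective n per arm | Power, pooled | Power, unpooled |
|---|---|---|---|---|---|
| 744 | 62 | 2.22 | 167.6 | 80.1% | 80.8% |
| 715 | 59.6 | 2.172 | 164.6 | 79.4% | 80.1% |

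The loss is about 0.7 percentage points in either form. It is small because the design effect shrinks along with the site size. The pooled form fits the article better: 62 is the smallest whole site size at which it reaches 80% (61 per site gives 79.9%), whereas the unpooled form already reaches 80% at 60 per site.

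**5. Per-arm figure.** 744 / 2 = 372, while 2 × 373 = 746. The total agrees with 12 × 62, which points to 372.

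**The case against.** **The consequence is negligible.** Power moves by about 0.7 points, and with unpooled variance it stays at 80.1%, so the 80% claim could be said to survive. This stands as to size. The article names no formula, so neither pair of power figures can be called its own; both depend on the assumptions listed above. It does not remove the mismatch between target and attrition, which needs no power formula.

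**The target is loose.** Setting says around 75 per site, and all eligible Registered Midwives may take part, so 894 is not a cap. This is fair, but 75 per site still leaves 720 after 20% loss.

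**Lost midwives may still contribute.** The Statistical analysis section plans intention-to-treat, generalised estimating equations on six-monthly surveys, and multiple imputation. This limits the practical effect further. It does not justify the factor of 1.2, because the Sample size section itself treats attrition as reducing the number available.

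**The per-arm slip is trivial and its direction is not settled.** This is also fair: 373 × 1.2 = 447.6, cut to 447, would lead to 894 as well. The bare 447 clearly means per arm, since 2 × 447 = 894.

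A reader might go further and infer that the sample size as a whole is wrong, or that the trial is materially underpowered because of this step. The article does not support either reading: 744 is reproduced from its inputs, only the inflation step fails, and the resulting loss is under one percentage point.

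**Conclusion.** The point holds as a minor arithmetic error. The step from 744 to 894 is consistent with multiplying by 1.2 and not with a 20% loss. The target is 36 below the 930 that the stated assumption requires, leaves about 715 analysable midwives in place of 744, and covers 16.8% attrition.

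These counts rest only on the article's own figures and the ordinary meaning of attrition. The power change, about 80.1% to 79.4% (pooled) or 80.8% to 80.1% (unpooled), rests in addition on a two-sided test, an absolute 15-point fall, an ICC of 0.02, equal site sizes and a normal approximation. No planned estimate or test changes. The disagreement between 373 and 744 is a slip of two midwives in total and adds no weight.

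**What to change.** Change the Sample size and Setting sections together, by one of two routes:

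- **Keep 894** and state that it allows for 16.8% attrition, adding that a 20% loss would leave about 715 analysable midwives and about 79.4% power, with the assumptions behind that figure. This is a change of wording only.
- **Raise the target to 930** (465 per arm, 77.5 or about 78 per site). This means 36 more midwives, or 3 more per site on average. Whether the sites can supply them cannot be judged here, since the article gives no site headcounts.

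Under either route, reconcile the per-arm 373 with the total of 744 (12 × 62 = 744 implies 372), and label the per-arm target as such: 447 per arm if 894 is kept, 465 per arm if the target is raised.
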